### **3 STUDY OBJECTIVES**

- To evaluate whether 7-day treatment with oral QLT091001 can improve visual function in subjects with LCA or RP caused by *RPE65* or *LRAT* gene mutations.
- To evaluate duration of visual function improvement (if observed) in subjects with LCA or RP caused by *RPE65* or *LRAT* gene mutations after 7-day treatment with oral QLT091001.
- To evaluate the safety of oral QLT091001 administered once daily for 7 days in subjects with LCA or RP caused by *RPE65* or *LRAT* gene mutations.

### **4 INVESTIGATIONAL PLAN**

#### **4.1 Overall Study Design**

This will be an open-label, proof-of-concept, phase 1b study. The study will include up to 28 subjects with LCA or RP due to inherited deficiency of *RPE65* or *LRAT* (up to 14 subjects for each disease cohort). Subjects in each disease cohort (including 2 gene mutation subgroups) will receive a once-daily oral loading dose of 40 mg/m^2 QLT091001 for 7 consecutive days, which was the maximum dose assessed in study RET HV 01 (see Figure 4). Subjects with either LCA or RP will be enrolled at 1 study center in Canada. A maximum of 5 subjects with RP will be enrolled at 2-3 study centers in the US. Adult subjects with RP will be enrolled at approximately 3 study centers in the EU.

**FIGURE 4. Study Design Schematic**

[figure not shown]

Subjects will be treated on an outpatient basis but will receive study treatment in the research clinic under medical supervision for each day of treatment. During the study treatment period and for 7 days post-treatment, subjects will be required to limit vigorous physical activity and also must follow dietary guidelines intended to avoid excessive vitamin A intake.

To determine proof-of-concept and safety, subjects will have the following ocular examinations (on both eyes) performed before and after treatment:

1. Best-corrected visual acuity (BCVA) using ETDRS (monocular and binocular tests)
2. Color vision

3. Visual field
4. Full-field ERG
5. OCT and FAF
6. Dynamic pupillometry and nystagmus testing (if instrument is available)

Safety evaluations will include monitoring of vital signs, ECG, clinical laboratory tests (12-hour fasting serum chemistry and hematology, serum retinol, coagulation testing, thyroid function testing, and urinalysis), biomicroscopy, IOP, dilated fundus examination, AEs, and concomitant medications.

Additionally, a subject questionnaire will be given to the subject and/or parent/guardian (if applicable) for completion at Screening and at follow-up visits starting at Day 14/15. Follow-up visits will continue through 12 months post-treatment, although subjects will complete the study at the Day 30 visit, or at any visit after that, if they meet entry criteria and are enrolled into a subsequent study for retreatment.

## **4.2 Discussion of Study Design**

The efficacy variables being used for this study are intended to generate results that are relatively stable over the very short time period during which each subject is treated during the study (7 days) and should therefore only change if there is a treatment effect. Subjects will be followed up for at least 12 months after treatment to assess the duration of treatment effect, as well as any potential delayed treatment effect. In preliminary data from this study, beneficial treatment effects have been observed in some subjects in at least 1 vision function measurement, but the duration of treatment effect is unclear, as is the timing of the onset of treatment effect [48]. Beneficial treatment effects need to be clear and clinically relevant if the treatment is to be developed further. The study does not include a control group, so each subject's baseline visual function will serve as the control for that subject.

Each subject will undergo daily treatments for 7 days, as it is believed that it will take at least 7 days for adequate amounts of QLT091001 and its precursor 9-*cis*-retinol to accumulate in the retina. However, a visual acuity test using best-corrected ETDRS is planned 24 hours after the first dose to evaluate whether a clinical effect of treatment occurs more rapidly.

### **4.2.1 Rationale for Selection of Vision/Efficacy Tests**

No single test has been validated to definitively evaluate the response of treatment for LCA or RP. One potential benefit of the vision tests selected for this study will be identification of a primary endpoint for subsequent trials, if a beneficial treatment effect is observed.

While ERG testing is the gold standard for evaluating therapeutic levels of several experimental therapies and is used routinely to diagnose and monitor progression of most inherited retinal diseases including LCA, ERG testing has not yet been correlated with endpoints accepted by regulatory agencies, such as ETDRS vision and Humphrey Visual Field Analyzer (HFA). A limitation of full-field ERG is that the recording is a massed potential from the whole retina. Unless 20% or more of the retina is affected with a diseased

state, ERG recordings are usually normal (e.g., a legally blind person with macular degeneration, enlarged blind spot or other central scotomas has normal global ERGs). Most LCA and RP subjects have virtually no measurable ERG recordings, yet many of these subjects can still see, some quite well. Recent gene therapy trials for LCA have not reported changes in full-field ERG results because the methods in these trials treated less than 10% of the retina, so the ERG results would not be expected to change.

A method for quantitative analysis of Goldmann visual field (GVF) is being developed and has shown promise as an endpoint in subjects with LCA and RP in the current study, as described in the IB. (GVF has been used instead of HFA because HFA is usually not appropriate for young subjects and subjects with very low vision.) This GVF analysis is incorporated into the study for assessment as a potential primary endpoint for future trials (see [Section 11.4](#)).

## 5 SELECTION AND WITHDRAWAL OF SUBJECTS

### 5.1 Number of Subjects

Up to 28 subjects in total will be enrolled in this study. This includes up to 7 subjects with LCA for each genotype subgroup (*RPE65* or *LRAT* mutations) and up to 7 subjects with RP for each genotype subgroup (*RPE65* or *LRAT* mutations). A maximum of 5 subjects with RP will be enrolled in the US. Subjects from outside of North America and Europe are eligible and will be required to travel to a study center to participate in the study.

### 5.2 Inclusion Criteria

To be eligible for the study, subjects must fulfill all of the following criteria:

1. Subjects will have either LCA or RP, with a mutation in either *RPE65* or *LRAT*, as follows:
  - a. Subjects with LCA will be 5-65 years of age diagnosed with LCA by an ocular geneticist or pediatric ophthalmologist.
  - b. Subjects with RP will be diagnosed with RP by an ocular geneticist or ophthalmologist and be:  
For Canada, Germany, The Netherlands, and UK: 18-65 years of age (inclusive).  
For US only: 8-65 years of age (inclusive).
2. Subjects who have a best-corrected standard ETDRS visual acuity of **3 letters** or better (**20/800 Snellen equivalent**), however; subjects with a lower ETDRS score will be eligible if spectral domain OCT and FAF reveals evidence of a viable photoreceptor layer.
3. Subjects who are girls or women of child-bearing potential must not be pregnant or lactating, must have negative serum pregnancy tests ( $\geq 25$  mIU/mL sensitivity) at Screening (i.e.,  $\geq 19$  days before Day -1, and on Day -1) and must have been practicing 2 adequate methods of birth control or complete abstinence for at least 2 months.

Adequate methods of birth control include (1) use of oral contraceptives (excluding low-dose oral formulation), implantable or injectable contraceptives, or an intrauterine device (IUD), with an additional barrier method (diaphragm with spermicidal gel OR condoms with spermicide); (2) a double-barrier method (diaphragm with spermicidal gel AND condoms with spermicide); (3) partner vasectomy; and (4) total abstinence.

4. Subjects who are boys or men must (1) agree to completely abstain from sexual intercourse, (2) have had a vasectomy, or (3) use a barrier method (condoms) with spermicide during sexual intercourse, during the treatment phase of the study and for 2 months after finishing the study drug.
5. Subjects who provide informed consent and, if applicable, assent for the study (applies to subjects 7 years and older). The parent or guardian must sign an approved informed consent form for the study for subjects younger than the age of majority.

Note that use of the term "subject" throughout this protocol may also include the parent/guardian of subjects younger than the age of majority, as appropriate.

6. Subjects who are willing to comply with the protocol.

### **5.3 Exclusion Criteria**

Subjects meeting any of the following criteria will be excluded from the study:

1. Subjects who are actively participating in an experimental therapy study or who have received experimental therapy within 60 days of Day 0.
2. Subjects with any clinically important abnormal physical finding at Screening.
3. Subjects who have taken any prescription or investigational oral retinoid medication (e.g., Accutane/Roaccutane® or Soriatane/Neotigason®) within 6 months of Day 0 and subjects who did not tolerate their previous oral retinoid medication will be excluded regardless of the time of last exposure.
4. Subjects with a history of diabetes or chronic hyperlipidemia, hepatitis, pancreatitis, or cirrhosis.
5. Subjects with liver failure, uncontrolled thyroid disease, hypersensitivity to retinoids, or hypervitaminosis A.
6. Subjects with any of the following findings at Screening:
  - Untreated blood pressure 150/95 mm Hg or higher upon repeated measurement
  - Resting heart rate <40 bpm or >100 bpm upon repeated measurement
  - ALT or AST >3 times the upper limit of the clinical laboratory value normal range upon repeated measurement
  - Total cholesterol, triglycerides, HDL, or LDL >2 times the upper limit of the clinical laboratory value normal range upon repeated measurement
  - Thyroid function tests outside the clinical laboratory value normal range upon repeated measurement

- Serum retinol clinical laboratory value above 90 µg/dL upon repeated measurement
- 7. Subjects with a documented and known allergy to soy.
- 8. Subjects who, in the Investigator's opinion, have any severe acute or chronic medical condition, psychiatric condition, or laboratory abnormality that may increase the risk associated with study participation or administration of study treatment, or interfere with the interpretation of study results.
- 9. Subjects with a marked baseline prolongation of QT/QTc intervals (e.g., repeated demonstration of a QTc interval >450 milliseconds [ms]).
- 10. Subjects with a history of additional risk factors for torsade de pointes (TdP) (e.g., heart failure, hypokalemia, history or family history of Long QT Syndrome), and Wolff-Parkinson-White (WPW) syndrome.
- 11. Subjects who have taken any supplements containing  $\geq 10,000$  IU vitamin A within 60 days of Screening.

#### **5.4 Withdrawal of Subjects**

Every effort will be made to have all subjects attend all study visits and receive all doses of study drug. Subjects can voluntarily withdraw from study treatment at any time during the study. Every effort will be made to complete study follow-up procedures if subjects terminate the study treatment early. In addition, Investigators may withdraw a subject from study treatment because:

- a new health condition appears that is suspected to require care or medications prohibited by the protocol
- the subject has unacceptable adverse events (AEs)
- the subject has clinical laboratory results as follows:
  - any hematology parameter (as listed in [Table 4](#), [Section 9.4.4](#)) that changes by more than 10% above the upper limit of the clinical laboratory value normal range
  - ALT or AST >3 times the upper limit of the clinical laboratory value normal range
  - total cholesterol, triglycerides, HDL, or LDL >2 times the upper limit of the clinical laboratory value normal range
  - thyroid function tests outside the clinical laboratory value normal range
  - serum retinol clinical laboratory value above 90 µg/dL
- the subject has a hypersensitivity reaction to study treatment (immediate withdrawal)
- the subject exhibits clinical signs of hypervitaminosis A, particularly if symptoms occur that indicate an increase in intracranial pressure (immediate withdrawal)
- there is a marked prolongation of the QT/QTc interval, such that

- it is >500 ms or increases >60 ms from baseline when the measurement obtained is averaged from the triplicate ECGs (see Section 9.4.3) (immediate withdrawal), or
  - in the Investigator's judgment an otherwise marked prolongation may indicate that the subject's safety is in jeopardy.
- it is in the subject's best interest according to the Investigator's clinical judgment

Subjects with the conditions or findings listed above will be considered for withdrawal from study treatment. Withdrawal for the reasons noted above will be reviewed in consultation with the medical monitor (refer to [Section 10.3](#)).

If a subject prematurely withdraws from study treatment, the reason(s) for withdrawal must be recorded on the relevant page of the subject's case report form (CRF).

See [Section 9](#) for details on study follow-up procedures and [Section 10.5](#) for details on follow-up for AEs. The Investigator should review the follow-up procedures with the subject and his/her parent(s)/guardian(s) if applicable, including the number of visits, the specific procedures to be done, and the total length of the follow-up period. The Investigator must also ensure it is understood that the subject's medical records will continue to be available for the follow-up period as described in the approved informed consent form for the entire study period.

If a subject refuses to undergo the study follow-up procedures, or his/her parent(s)/guardian(s) refuses to allow the subject to undergo the procedures, the reason for refusal should be fully documented. Subjects who do not continue study procedures should undergo all end-of-study assessments.

Subjects who miss study drug doses will continue to be followed up in the study. Additional subjects may be enrolled to replace subjects who withdraw before completing adequate study follow-up or to supplement data if several subjects miss doses of study drug.

Subjects will withdraw from the study follow-up procedures on Day 30 or at a subsequent visit, and be considered to have completed the study, if they meet entry criteria and are enrolled in a subsequent retreatment study (see [Section 1](#)).

The Sponsor may stop the study at any time.

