### **1.5 Study RET HV 01 (Safety, First in Humans)**

Study RET HV 01 was conducted to investigate the safety and tolerability of daily oral doses of QLT091001 for 7 days in 6 dose level cohorts of healthy adult volunteers. Three subjects were included in each dose cohort with the exception of the highest dose cohort which included 5 subjects. Doses escalating from 1.25 mg/m^2 to 40 mg/m^2 were tested in series approximately 2-3 weeks apart through a doubling process (1.25 to 2.5 to 5.0 to 10 mg/m^2 etc.). For each dose cohort, extensive laboratory tests and vital signs were evaluated at Screening, the evening before dosing, the next morning shortly before the initial dose, and at regular intervals during and after the 7-day dosing period. AEs were evaluated at every visit beginning on Day 1. Holter monitoring was done at Screening, 24 hours following the first dose, and the day after the last dose; ECGs were done at Screening, the day before the initial dose, before and after dose 3, and 3 days after the last dose. When all test results up to 3 days after the seventh dose were available for a specific cohort, a safety monitoring committee reviewed the information before dose escalation was allowed for the next cohort.

In the cohorts dosed with 10 to 40 mg/m^2, a reduction of plasma high density lipoprotein (HDL) concentrations was observed in most subjects. This HDL reduction did not appear to be dose-dependent and was rarely out of the normal-low range. Some of these subjects also had milder reductions of plasma low density lipoprotein (LDL) concentrations. Isolated reductions in one or more hematologic parameters (hemoglobin, red blood cells, hematocrit) were also noted in 2 subjects (1 subject who took the 5 mg/m^2 dose and 1 who took the 40 mg/m^2 dose) but these events were mild and not considered to be clinically significant. Drug-related adverse symptoms only occurred in the 5 subjects receiving 40 mg/m^2 who all

reported mild headache(s); some subjects also reported mild facial flushing (2/5) and mild loss of appetite (2/5) and 1 subject reported moderate nausea. These AEs were noted during the first 4 days of dosing and resolved thereafter.

Overall, 7 daily oral doses of QLT091001 up to 40 mg/m^2 were well tolerated. A more complete description of this study is provided in the Investigator Brochure (IB).

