### 8.3 Anticipated Clinical Effects Based on Clinical Studies

See [Section 1.5](#) for a description of results from the RET HV 01 study. In the current ongoing study (RET IRD 01), preliminary safety data from a total of 14 subjects treated with QLT091001 (12 received 40 mg/m^2 and 2 received 10 mg/m^2) was assessed. In these studies, adverse effects included the following, which may be potential risks with the study drug:

- GI Disorders: nausea
- General Disorders and Administration Site Conditions: asthenia, facial flushing
- Metabolism and Nutrition Disorders: decreased appetite
- Nervous System Disorders: facial burning sensation, headache, photophobia, dizziness
- Investigations: hemoglobin decreased, RBC count decreased, increased triglycerides, decreased HDL, increased or decreased LDL, increased cholesterol, increased AST

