**TABLE 4. Clinical Laboratory Tests**

| Hematology                                                                                                                                                  | Serum Chemistry                                                                                                                                                                                                                                                                                             | Urinalysis                                                                                                                                                                                          | Other Tests                                                                |
|--------------------------------------------------------------------------------------------------------------------------------------------------------------------|--------------------------------------------------------------------------------------------------------------------------------------------------------------------------------------------------------------------------------------------------------------------------------------------------------------------|------------------------------------------------------------------------------------------------------------------------------------------------------------------------------------------------------------|-----------------------------------------------------------------------------------|
| - Hemoglobin
- Hematocrit
- White blood cell count
- Differential
- Red blood cell count
- Platelet count
- Coagulation testing:
PT/INR, APTT | - Sodium
- Potassium
- Calcium
- BUN
- Creatinine
- Total cholesterol
- Total protein
- Albumin
- ALT
- AST
- Alkaline phosphatase
- Total bilirubin
- Direct bilirubin
- Glucose
- TG
- HDL
- LDL
- Chloride
- Bicarbonate
- Inorganic phosphate testing | - Dipstick
- Specific gravity
- pH
- Protein
- Glucose
- Ketones
- Bilirubin
- Blood
- Urobilirubin
- Urinalysis
- Microscopic urinalysis if urinalysis results are abnormal | - Thyroid function testing:
- free T3
- free T4
- TSH
- Serum retinol |

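### The hematology criterion for considering withdrawal (Protocol 5.4) has only an upper limit, although the only red-cell effects the protocol reports are decreases

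*Protocol*

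**What the plan says.** Section 5.4 of the protocol lists reasons for which an investigator may withdraw a subject from study treatment. One is any hematology parameter in Table 4 "that changes by more than 10% above the upper limit of the clinical laboratory value normal range". Table 4 (Section 9.4.4) puts hemoglobin, hematocrit, "Red blood cell count", white cells with differential, platelets, PT/INR and APTT in its hematology column.

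Two sentences after the list set its force: "Subjects with the conditions or findings listed above will be considered for withdrawal from study treatment", and "Withdrawal for the reasons noted above will be reviewed in consultation with the medical monitor".

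On red-cell effects in humans, Section 1.5 says of the healthy volunteer study: "Isolated reductions in one or more hematologic parameters (hemoglobin, red blood cells, hematocrit) were also noted in 2 subjects". One of the two took 5 mg/m² and the other 40 mg/m², the dose used here. The section adds that "these events were mild and not considered to be clinically significant". Section 8.3 combines that study with preliminary data from the present one and includes "hemoglobin decreased, RBC count decreased" among the potential risks. No rise in a red-cell parameter is reported in either section.

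**The concern.** The bullet covers every hematology parameter but can be met in one direction only. For hemoglobin, hematocrit and red cell count, that is the direction in which the protocol reports no effect. The thyroid bullet in the same list, "thyroid function tests outside the clinical laboratory value normal range", works both ways.

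What is at stake is consistency. A rise has a common number that brings the subject up for consideration. A fall has none, so whether it is raised depends on each investigator's judgment. The study has centers in Canada, the US and the EU (Section 4.1), uses local laboratories (Section 9.4.4) and is the first to give the drug to children (Section 2.2).

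**Working it through.** **1. What the criterion can detect.** Write U and L for the upper and lower limits of normal. The bullet is met when the value exceeds 1.10 × U. A value below L is below U and therefore below 1.10 × U, so no value under the normal range can meet it, whatever the range is. The documents give no laboratory ranges. As an illustration only, assume hemoglobin 120–160 g/L:

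- Criterion met above 1.10 × 160 = 176 g/L.
- Values of 100, 80 or 60 g/L do not meet it.

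**2. Direction of the reported effects against direction of the limit.**

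| Parameter | Reported direction | Section 5.4 limit |
|---|---|---|
| Hemoglobin | Down (Sections 1.5, 8.3) | Upper only |
| Red cell count | Down (Sections 1.5, 8.3) | Upper only |
| Hematocrit | Down (Section 1.5) | Upper only |
| PT/INR, APTT | Prothrombin time up, as a vitamin A effect (Table 2, Section 8.1) | Upper only |

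The limit suits the coagulation tests and not the red-cell tests.

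**3. Is a lower-side number given elsewhere?** No. Section 10.4 refers back to the Section 5.4 criteria. Section 7.3 leaves dose reduction to the investigator. Section 5.3 sets no numeric hematology limit at entry, so a subject may start low.

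**4. How often red-cell reductions were seen.** Section 1.5 describes five cohorts of 3 and one of 5, so 5 × 3 + 5 = 20 volunteers.

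- Any reduction: 2/20 = 10% (exact 95% CI 1.2% to 31.7%), pooled over doses from 1.25 to 40 mg/m².
- At 40 mg/m²: 1/5 = 20% (exact 95% CI 0.5% to 71.6%).

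These count reductions of any size, and both were mild. The documents do not say how large they were, so the rate of falls beyond 10% below L is unknown.

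**5. How many subjects and doses a change could reach.**

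- Subjects: 28 planned, and Section 8.3 describes 14 already treated. 28 − 14 = 14 at most, apart from replacements under Section 5.4.
- Doses: seven, on Days 0–6. The only scheduled hematology draw during dosing is predose on Day 3 (Table 3, footnote i). Three doses (Days 0–2) come before it, leaving 7 − 3 = 4, or 3 if the result arrives after the Day 3 dose.

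**The case against.** The strongest reply is that little depends on this bullet. Withdrawal under the list is permissive. Medical-monitor review attaches to withdrawal for any listed reason, including unacceptable adverse events and the subject's best interest, so a subject withdrawn for a red-cell fall on those grounds gets the same review. Clinically significant laboratory results must be recorded as adverse events (Sections 9.4.4 and 10), and the dose can be reduced (Section 7.3). Section 8.2 names liver, bone and heart as the target organs, not blood. The two volunteer reductions show no visible dose relation. Most of the other laboratory limits in the list (transaminases, lipids, serum retinol) are also upper-side, including the one for HDL, although Section 1.5 reports HDL reductions in most subjects at 10 to 40 mg/m².

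All of this stands as a limit on the consequence. It does not supply the missing direction: each alternative route starts from individual judgment, which the numeric bullet was there to supplement. That other limits are also upper-side does not make this one fit hemoglobin, hematocrit or red cells.

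A reader might go further and infer that the plan leaves a subject with a serious fall in hemoglobin without protection. The routes just listed contradict that. A reader might also multiply the volunteer percentages by 28 to forecast affected subjects. That does not hold: 14 subjects had already been treated, and the percentages count any reduction, not one beyond a threshold.

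**Conclusion.** The point holds and is minor. As worded, the hematology bullet cannot be met by a fall in hemoglobin, hematocrit or red cell count, and decreases are the only red-cell effects the protocol reports. What is lost is an objective, common prompt to consider withdrawal, not the ability to act on a harmful fall.

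A change could affect at most about 14 further subjects and, through the scheduled Day 3 draw, at most 4 of a subject's 7 doses. The number who would cross a lower threshold cannot be estimated from the documents. The figure of 14 assumes that the treated subjects in Section 8.3 count toward the planned 28 and that no replacements are enrolled. The direction argument needs no assumption about normal ranges.

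**What to change.** Reword the one bullet in Section 5.4 at the next amendment, for example:

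*Any hematology parameter (Table 4) more than 10% above the upper limit of the normal range, or hemoglobin, hematocrit or red blood cell count more than 10% below the lower limit of the normal range; for a subject already below that level at Day -2/-1, a further fall of more than 10% from the Day -2/-1 value.*

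The last clause is needed because entry is not restricted by a hematology limit. Without a minimum fall, a subject who starts low would be flagged by assay noise. With the assumed 120–160 g/L range, the lower threshold is 0.90 × 120 = 108 g/L, and a subject starting at 105 g/L would be flagged below 0.90 × 105 = 94.5 g/L. The lower-side term is confined to the three parameters with reported falls; the other hematology tests keep their upper limit.

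Section 10.4 points to Section 5.4 and needs no edit. Hematology is already drawn at Screening and on Day -2/-1, Day 3 and Day 7/8, so no samples or visits are added. The cost is an occasional extra consultation with the medical monitor.

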## 1 INTRODUCTION AND BACKGROUND

This will be a phase 1b study to investigate the safety, tolerability, and proof-of-concept for oral QLT091001 as a new treatment for subjects with Leber Congenital Amaurosis (LCA) or retinitis pigmentosa (RP) due to inherited mutations in *RPE65* (encoding the protein retinal pigment epithelial protein 65) or *LRAT* (encoding the enzyme lecithin:retinol acyltransferase). The study will be conducted in compliance with the protocol, International Conference on Harmonization (ICH) good clinical practice (GCP) guidelines, and Part C, Division 5 of the Canadian Food and Drug Regulations.

Subjects with either LCA or RP will be enrolled in 1 study center in Canada, a maximum of 5 subjects with RP will be enrolled at approximately 2-3 study centers in the United States, and adult subjects with RP will be enrolled at approximately 3 study centers in the European Union.

In Canada, this protocol is associated with addendum protocol RET IRD 01 (fMRI), which describes functional magnetic resonance imaging (fMRI) procedures to be done in conjunction with this main protocol, if feasible and if separate informed consent is obtained. Please refer to addendum protocol RET IRD 01 (fMRI) for more information.

Study RET IRD 01 will be associated with a subsequent retreatment protocol, which will enroll subjects from RET IRD 01 who meet entry criteria for retreatment.

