## 9.3 Treatment and Follow-up Procedures

Treatment and follow-up procedures will be done as identified in [Table 3](#).

On Day 0, each subject will receive the first dose of study drug. Treatment will be administered for 7 consecutive days (Day 0 to Day 6, inclusive).

Subjects will have follow-up visits on Days 7/8, 14/15 and 30; and Months 2, 4, 6, 8, 10, and 12. All visual function and safety assessments will be done on Day 7/8 (24/48 hours after taking the last dose of study drug). Visual function tests and safety assessments will be done on Day 14/15 and each subsequent visit. Women and girls of child-bearing potential will have urine pregnancy tests on Day 14/15, Day 30, and Month 2. AEs and concomitant medications will be monitored at every visit. The subject questionnaire will be completed on Day 14/15 and every subsequent visit. These procedures are described further in [Sections 9.4, 9.5, 9.6, and 9.7](#).

All efforts will be made for subjects to comply with the follow-up visit schedule. However, if the schedule is not feasible for a subject, follow-up visits will be conducted as closely to the schedule as possible.

Subjects will complete the study at the Day 30 visit, or any subsequent visit, if they meet entry criteria and are enrolled into a subsequent retreatment study (see [Section 1](#)).

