### 11.4.1 Best-Corrected Visual Acuity Using ETDRS Testing

Visual acuity scores based on ETDRS testing and changes from baseline will be provided for each time point by gene mutation subgroup and disease cohort using descriptive statistics (mean, standard deviation, minimum, median, and maximum).

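### Subjects may leave from Day 30 for retreatment, which contradicts the stated 12 months of follow-up and can make the Month 2 to 12 by-visit summaries misstate duration of effect in either direction

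*Protocol*

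**What the plan says.** Section 3 lists duration as the second of three objectives: "To evaluate duration of visual function improvement (if observed) in subjects with LCA or RP". Section 4.2 ties the follow-up period to it: "Subjects will be followed up for at least 12 months after treatment to assess the duration of treatment effect". Section 9.3 sets the visits: "Subjects will have follow-up visits on Days 7/8, 14/15 and 30; and Months 2, 4, 6, 8, 10, and 12".

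Section 5.4 provides an earlier end: "Subjects will withdraw from the study follow-up procedures on Day 30 or at a subsequent visit, and be considered to have completed the study". This applies to anyone who qualifies for the later retreatment protocol and joins it. Sections 4.1 and 9.3 and the Protocol Summary repeat this exit. The criteria belong to a separate protocol, described in Section 1 only as one "which will enroll subjects from RET IRD 01 who meet entry criteria for retreatment".

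The stated efficacy analyses are descriptive. For visual acuity, Section 11.4.1 says that "changes from baseline will be provided for each time point by gene mutation subgroup and disease cohort", using mean, standard deviation, minimum, median and maximum. Section 11.4.4 summarizes the remaining variables by subgroup, cohort and visit. Sections 11.4.2 (ERG) and 11.4.3 (Goldmann field) plan descriptive summaries of change from baseline but do not say that they are by visit. Section 11.4 evaluates each eye separately.

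**The concern.** Section 4.2 and the exit rule disagree about how long subjects are observed, and the disagreement falls on the one feature of the design meant to answer the duration objective. Once a subject is retreated, the later course after a single 7-day treatment can no longer be seen, whatever a statistical analysis plan says.

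The remaining subjects need not resemble those who left. If subjects whose gain has faded leave for retreatment, the late mean stays high and the effect looks lasting. If subjects who responded leave while their gain persists, the late mean drops and the effect looks short-lived. There is no control group to show which has happened.

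**Working it through.** **1. The follow-up statements side by side.** Section 4.2 gives at least 12 months. Sections 4.1, 5.4 and 9.3 allow completion at Day 30 or any later visit on enrolment into retreatment. A subject who exits at Day 30 satisfies the second and breaks the first. Section 5.4 allows replacement of subjects who withdraw before adequate follow-up. Retreatment leavers are classed as having completed, so that provision does not clearly reach them.

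**2. Numbers per cell.** Section 11.1 gives 7 subjects per genotype per disease cohort: 2 × 2 × 7 = 28, which reproduces the stated total. The half-width of a 95% confidence interval for a mean, in SD units, is t(0.975, n−1)/√n:
- n = 7: 2.447/2.646 = 0.92
- n = 4: 3.182/2 = 1.59
- n = 3: 4.303/1.732 = 2.48

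A few exits therefore leave little to summarize in a cell, even without bias.

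**3. Can selective exit move the by-visit mean?** The protocol gives no effect size, SD, waning rate, exit rate or retreatment criteria, so every input here is an assumption. Day 30 gain is Normal with mean 8 and SD 8 letters. The gain at month t is the Day 30 gain × exp(−(t−1)/τ), with τ log-normal (median 6 months, log-SD 0.7). Measurement SD is 3 letters. After each visit from Day 30, an eligible subject leaves with probability p. Over 20,000 simulated trials, the mean gain with everyone followed is 3.4 letters at Month 6 and 1.6 at Month 12. The mean among those still present, and the number left of 7, are:

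| Assumed rule for leaving | p | Month 6 mean | Month 12 mean | Left at Month 6 | Left at Month 12 |
|---|---|---|---|---|---|
| Current gain 5 letters or more | 0.3 | 2.1 | 0.6 | 4.3 | 3.6 |
| Same | 0.6 | 0.6 | −0.1 | 2.8 | 2.3 |
| Current gain under 5 letters | 0.3 | 4.7 | 3.2 | 4.8 | 2.6 |
| Same | 0.6 | 6.0 | 5.1 | 3.5 | 1.2 |
| Day 30 gain of 5 or more, now under half of it | 0.3 | 3.4 | 1.5 | 6.2 | 4.4 |
| Same | 0.6 | 3.4 | 1.3 | 5.5 | 3.4 |
| Unrelated to vision | 0.3 | 3.4 | 1.6 | 2.4 | 0.8 |
| Same | 0.6 | 3.4 | 1.5 | 0.4 | 0.0 |

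The largest errors are 0.6 − 3.4 = −2.8 and 6.0 − 3.4 = +2.6 letters at Month 6, and −0.1 − 1.6 = −1.7 and 5.1 − 1.6 = +3.5 at Month 12. Two rules give little or no error. The 1.5 in the last row is simulation noise with almost nobody left.

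**4. Would a curve censored at exit solve it?** Not by itself. Censoring assumes that leavers would have lost their gain at the same rate as stayers. With assumed responders (mean gain about 10 letters, median half-life 3 months, loss defined as falling below 4 letters) and subjects with a gain of 6 or more leaving with probability 0.5 per visit, the proportions still improved are:

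| | True | Censored at exit | Loss at exit |
|---|---|---|---|
| Month 4 | 0.44 | 0.27 | 0.09 |
| Month 6 | 0.24 | 0.11 | 0.03 |

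Both displays lie below the truth. What matters is the order, not the values. An upper bound needs a third display in which a gain present at exit is taken to persist.

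**The case against.** The strongest reply has four parts.

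First, definitions of duration, censoring rules and numbers at risk are commonly left to a statistical analysis plan, which is not shown here. This stands: a reader might infer that the duration objective cannot be answered, but Section 11.4 does not exclude a per-subject or per-eye duration summary. A later plan cannot, however, reconcile Section 4.2 with Section 5.4 or recover observations lost at exit.

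Second, the bias depends on criteria in another protocol. This also stands. A reader might infer that the Month 2 to 12 results are biased. The document supports only that they can be, and the last two rules in the first table show little or no bias.

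Third, a reader might infer that calling leavers completers hides them. The document does not support that. Table 3 has a separate row for completion on enrolment into the extension study, and the exit is stated openly in several sections. Visual acuity, color vision and visual field testing are scheduled at Day 30 and every later visit, so the course up to exit is largely kept. ERG after Day 30 is at the investigator's discretion.

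Fourth, this is a small, open-label, descriptive phase 1b study with no hypothesis test. That lowers the severity but does not remove the contradiction.

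**Conclusion.** The concern holds in a limited form. The contradiction between Section 4.2 and Sections 4.1, 5.4 and 9.3 is certain and needs no assumption. The risk to the duration objective is conditional: if entry to retreatment is related to visual response, the by-visit summaries in Sections 11.4.1 and 11.4.4 can misstate duration either way. The document does not allow the amount to be computed. The illustrated errors of about −2.8 to +2.6 letters at Month 6 rest wholly on the assumed gains, waning and exit rates, and shrink to about zero under other exit rules. The by-visit argument does not extend on the text to ERG or Goldmann field, whose summaries are not described as by visit. This should be fixed; it is not a fault that invalidates the study.

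**What to change.** Retreatment rules stay as they are.

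1. Reconcile Section 4.2 with Sections 4.1, 5.4 and 9.3. If the exit provision stands, Section 4.2 could describe follow-up as at least to Day 30 and up to 12 months.
2. Report exits to retreatment separately from 12-month completers, and give the number remaining and the number exited at each visit.
3. Add a per-eye duration summary to Section 11.4. Start the clock at the first visit with improvement beyond the pretreatment test-retest limit, not at a fixed day, because Section 4.2 anticipates delayed effects. End it at the first visit at which that improvement is lost, interval-censored between visits. Show exit to retreatment three ways: loss at exit (lower bound), persistence after exit (upper bound), and censored at exit (a middle display, not a bound). The bounds apply to eyes that had improved before exit; improvement that would have begun later remains unseen.
4. Tabulate response status at the exit visit from the visual acuity and visual field data already scheduled there.

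The cost is some wording and one extra table and figure, with no new assessments. Duration will be reported as a range, which may be wide if many subjects leave early.
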